### Sample size considerations

With two staff psychiatrists and a clinical coordinator, we expect an average of six patients to receive comprehensive psychiatric assessments at the RASP each working day. Thus, we anticipate that the total number of patients accessing the service over the 24-month data collection period would be at least 2500. We also expect the sample size for the control population (patients whom a primary care provider referred to the MHAP Central Intake Services between May 2020 and May 2022) to be at least equal to the numbers seen at the RASP over a similar two-year time frame. Therefore, the data set to be generated from an overall sample of 5000 patients in this study would be large. With the assumption that the implementation of RASP will lead to at least a 10% reduction in high-cost health services utilization one-year post initial referral from a primary care provider for patients attending the service compared to patients who were offered a future appointment to see a mental health clinician as an entry point to the community mental health program, a power of 90% (β = 0.1) and a two-sided significance level of α = 0.05, and assuming an aggregated mean high cost health services utilization of 10 (SD =1) for the control population, we estimated that a sample size of 525 per group would be sufficient. Given that we expect at least 2500 patients per group in our study, it is highly probable that our study has more than sufficient power to detect the projected differences in high-intensity/cost health services utilization between the two groups.

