Similar concerns are related to frequent ED visits. Frequent ED visitors are commonly defined as people having 4 or more ED visits during the past 12 months [18], and they are more likely to suffer from chronic somatic diseases, drug and alcohol abuse and acute mental illness [18]. Predictors for recurrent ED visits due to acute mental health problems are usually substance abuse, single status and homelessness [19].

In addition to readmission rates and frequency of ED visits, length of stay (LOS) is another important quality of care indicator. LOS is defined as the number of days between admission and discharge dates for each admission experienced [20]. LOS is likely to be multifactorial, but some factors associated with longer LOS have been consistently identified: biological sex (being male), ethnicity (being Asian, Black, or having mixed background), accommodation status (being homeless) and having the primary diagnosis of psychosis. Although there is no ideal LOS, current international recommendations advocate for an early discharge as soon as stabilization is successful, with continuation of treatment in less restrictive environments [20]. On the contrary, concerns about prioritizing shorter stay admissions include increasing medical negligence and favouring the revolving door cycle, which can be aggravated with a history of repeated admission and frequent ED visits [20, 21].

Besides the high rates of health services utilization, mental disorders are associated with major social and economic consequences for patients and their families. Patients with mental disorders have high mortality rates [22], poor quality of life [23], lower self-esteem [24], and lack of educational and income-generating opportunities, thus limiting their chances of economic independence and depriving them of social networks and status within the community [14]. Individuals with mental disorders also experience a variety of chronic physical health problems, such as hypertension and cerebrovascular diseases [15]. Despite the pervasive need for mental health treatment among individuals with mental disorders, it is generally acknowledged that many do not use healthcare services [25].

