### Participants and data collection

All RASP patients receive a consent form as part of their intake process, allowing access to their health services utilization records. Only those who sign the consent form will be part of the study. While consent is obtained during the initial assessment for ongoing patient recruitment, data collection is scheduled to commence after the program's first year, in April 2024. Service utilization data will extracted from provincial information systems retrospectively and prospectively at 2-time points: one year pre- and one-year post-assessment date at RASP. In addition, sociodemographic and mental health assessment information, including results from patient-completed validated scales and psychiatry diagnosis, and patient satisfaction will be extracted from routine paper-based initial screening forms. Patient satisfaction quantitative data will be extracted from RASP's patient satisfaction survey, available in a paper-based format and completed immediately after the assessment or REDCap online survey link sent via text message to all patients attending the service just after the assessment appointment.

The control group for the cohort study will comprise patients referred to the MHAP Central Intake Services by a PHP before RASP implementation. The periods for inclusion in the control group will be May 2017 to May 2019 (pre-COVID) and May 2020 to May 2022 (during COVID). By examining the data from these two time points (pre-COVID and during COVID) and comparing them with each other and with data during the RASP implementation period, we will be able to evaluate the impact of the pandemic on health services utilization as well as the impact of RASP implementation in comparison with both the pre-pandemic and during the pandemic periods. Ethics approval for exemption from requiring informed consent for all control group patients has been granted by the Research Ethics Board at Nova Scotia Health (REB file #1028254), allowing control group patients' sociodemographic and health services utilization information from provincial administrative databases to be accessed by the investigators.

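### The stated sample-size inputs give about 22 patients per group, not 525, and the SD of 1 has no source, so the claim of more than sufficient power is unsupported

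*Protocol article*

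**What the plan says.** The calculation is under Sample size considerations in the Protocol article. It targets "at least a 10% reduction in high-cost health services utilization one-year post initial referral" in RASP patients compared with patients offered a later appointment with a mental health clinician. It sets 90% power and "a two-sided significance level of α = 0.05", and then gives the assumed aggregated mean and the result together: "utilization of 10 (SD =1) for the control population, we estimated that a sample size of 525 per group would be sufficient". No source is given for the mean or the SD.

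The section expects at least 2,500 patients per group over 24 months, a figure based on clinic throughput. Setting this against 525, it concludes that "it is highly probable that our study has more than sufficient power to detect the projected differences".

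Two other sections bear on this. Outcome measures lists mobile crisis visits, ED visits, admissions, readmissions and length of stay, in terms of frequency, duration and cost, and does not define an aggregate. Participants and data collection says of RASP patients: "Only those who sign the consent form will be part of the study".

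**The concern.** This is the plan's only quantitative power statement, and it stands behind the headline hypothesis of at least a 10% reduction in high-cost service use. All the ingredients of a two-group comparison of means are printed, so a reader can check it, and the printed result is about 24 times what they give (525/22). Something in the paragraph is wrong and the text does not show what.

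The SD matters most. It is one tenth of the mean, for an outcome built from visits, admissions and possibly days. If that value is a slip, the spread actually assumed is unknown. If it is intended, it needs evidence. Either way the step from 525 to ample power at 2,500 has no basis that can be checked. A result showing no clear difference could then be read with more confidence than the plan has earned.

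**Working it through.** **Inputs** (all from Sample size considerations): control mean 10; SD 1; reduction 10%; power 90%; two-sided alpha 0.05; equal groups; stated n = 525 per group; expected n at least 2,500 per group.

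**1. The plan's own figure.** Difference = 0.10 × 10 = 1, so d = 1/1 = 1.0.

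n per group = 2(1.960 + 1.2816)²/d² = 21.01/1² = 21.0, rounded up to 22. The t-test solution is 22.02, rounded up to 23. The stated 525 is not reproduced.

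**2. Variants, keeping difference 1 and SD 1.** One-sided: 18. Power 80%: 16. Power 95%: 26. Alpha 0.01: 30. Paired t-test: about 13. Inflating 22 for 10%, 20% or 50% dropout: 25, 28 or 44. None is near 525.

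**3. What 525 corresponds to.** Solving for d: (1.960 + 1.2816) × √(2/525) = 0.200. In the other direction, 21.01/0.2² gives 525.4 before the constant is rounded. At least three routes lead there:
- SD 5 with a difference of 1;
- SD 1 with a difference of 0.2, a 2% reduction from 10;
- a difference of 10 percentage points in a proportion at maximum binomial variance (SD 0.5), since 0.1/0.5 = 0.2.

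The text states a mean and an SD, so the third is not the calculation described, but it shows that the origin of 525 cannot be inferred.

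**4. The SD.** SD 1 is variance 1. A Poisson count with mean 10 has variance 10 and SD √10 = 3.16, which would need 21.01 × 10 = 210.1, so 211 per group. Patients who differ in their underlying rate of service use push the variance above Poisson, not below it.

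**5. What 2,500 per group can support.** For a 10% reduction only the ratio r = SD/mean matters. Power = Φ(0.1/(r√(2/2500)) − 1.96). Ninety percent power requires r ≤ 0.1 × √(2500/21.01) = 1.09. For 525 per group the limit is 0.1 × √(525/21.01) = 0.50. The text assumes 0.10.

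The SDs below are illustrative, apart from the stated SD of 1.

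| SD at the stated mean of 10 | SD/mean | n per group for 90% power | Power at 2,500 per group |
|---|---|---|---|
| 1 (as stated) | 0.10 | 22 | >99.9% |
| 5 | 0.50 | 526 | >99.9% |
| 10 | 1.00 | 2,102 | 94% |
| 10.9 | 1.09 | 2,497 | 90% |
| 12 | 1.20 | 3,027 | 84% |
| 15 | 1.50 | 4,729 | 65% |
| 20 | 2.00 | 8,406 | 42% |

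**6. Consent.** The documents give no consent rate. As an illustration only, suppose half of 2,500 RASP patients consent. Against 2,500 controls the equivalent equal group size is 2 × 1250 × 2500/3750 = 1,667, and the 90% limit on SD/mean becomes 0.1 × √(1667/21.01) = 0.89. If controls were also reduced to 1,250, for instance by one-to-one matching, it becomes 0.1 × √(1250/21.01) = 0.77.

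**The case against.** The best defence is that the error is harmless. If the printed inputs were right, 22 would suffice and 2,500 would look more ample, not less. The sample is set by throughput, not by this calculation, and 2,500 is described as a minimum. The planned ANCOVA uses prior-year utilisation as covariate; at an assumed correlation of 0.5 the 90% limit on SD/mean rises to 1.09/√(1 − 0.25) = 1.26. Participants and data collection also adds a second control period, 2017 to 2019. If controls numbered 5,000 (an assumption), the limit would again be about 1.26 without the covariate.

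All of this stands as an argument against calling the study underpowered. It does not repair the paragraph, whose numbers still disagree and whose conclusion still rests on an unsourced SD.

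Three stronger readings are tempting and are not supported:
- **The SD is impossible.** It is extreme under-dispersion and highly implausible, but the Poisson value is not a mathematical floor. Nor is it settled that the aggregate is a pure count, since the outcomes include duration and cost.
- **A mean of 10 is absurd against the Background's definition.** That definition reads "Frequent ED visitors are commonly defined as people having 4 or more ED visits during the past 12 months". It counts ED visits only, whereas the 10 is an aggregate over several services and may include inpatient days. The two are not comparable.
- **The study is underpowered.** Low power figures can be produced by assuming means of 0.5 to 2 and heavy over-dispersion, but the documents give neither. At the stated mean of 10, assuming variance = mean + k × mean², power at 2,500 per group is 92% for k = 1 (SD √110 = 10.5) and 68% for k = 2 (SD √210 = 14.5). The answer turns on a spread the documents do not report.

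**Conclusion.** The concern holds as an error in the stated calculation and an unsupported conclusion. The printed inputs give 22 per group (23 by t-test); 525 needs a standardised difference of 0.2, one fifth of the one implied. This part rests on no outside assumption.

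That the SD is highly implausible is a judgement about yearly service-use data. The documents contain no observed SD to test it against.

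Inadequate power is not established. The supportable statement is conditional: with 2,500 analysed per group and an unadjusted comparison of means, 90% power for a 10% reduction requires SD/mean of about 1.09 or less, and 80% power requires about 1.26 or less (SD 12.6 at mean 10). Whether the data meet this is unknown, and the consenting sample may be smaller than the number using the service.

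**What to change.** - State which input or standardised effect produced 525, and correct the paragraph so that mean, SD, difference and n agree. Substituting 22 for 525 is not enough, because it would keep the implausible SD.
- Take the mean and SD of one-year aggregated utilisation from the historical control records, which the investigators are already approved to access.
- Define the aggregate, including whether inpatient days are added to visits, so that the quantity powered can be matched to the listed outcomes.
- Restate power for the expected consenting sample as a short table over SD/mean, labelled illustrative and including the stated mean of 10.
- Replace the sentence claiming more than sufficient power with the condition that 90% power at 2,500 per group requires SD/mean of about 1.1 or less.

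The cost is rewording and one descriptive extract from the control data. No more patients are needed, and this fix leaves the design and analysis unchanged. The stated power may become less favourable.

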### Data analysis

#### Quantitative analysis

Quantitative data will be analyzed using descriptive and inferential statistics by using SPSS version 26 for Windows [46]. First, we will summarize the study participants' sociodemographic and clinical descriptive characteristics. Primary outcomes comparing the pre-and post-enrollment health services utilization for patients accessing RASP will be analyzed using descriptive and inferential statistical analysis, including Chi-Square and independent sample t-tests. For the primary outcome involving control populations, pre- and post-enrollment health services utilization variables will initially be compared using an analysis of covariance (ANCOVA) with the intervention condition (attended RASP) as the independent variable, the relevant health services utilization data one year pre attendance of appointment with RASP psychiatrist or community mental clinician as the covariate, and the relevant high-cost health services utilization data one year post attendance of appointment with a RASP psychiatrist or attendance with mental health clinicians in the community mental health program as the dependent variable. In each case, checks would be conducted to ensure no violation of regression slopes and reliable measurement of the covariate. We will perform sensitivity analyses of covariance to explore the impact of the imputation of data loss at each time point on health services utilization. In addition, we will perform propensity score matching and regression analyses adjusting for the periods pre-, during and post COVID-19 pandemic in order to strengthen the comparability of the groups and enhance the validity of the study's findings.

We will also use an ANCOVA to compare high-cost health services utilization data for one-year pre- and post-RASP attendance for the subset of patients who attend RASP and either participate or do not participate in the Text4Support RCT. For this analysis, the intervention condition (participants in the Text4Support RCT) will be the independent variable, the relevant health services utilization data one-year pre-attendance of appointment with RASP psychiatrist will be the covariate, and the relevant high-cost health services utilization data one-year post attendance of appointment with a RASP psychiatrist will be the dependent variable.

Using data from the first preliminary data analysis at the end of Year 2 and refining this at each subsequent analysis, we will perform regression to predict characteristics and risk factors for ED presentations for mental health concerns and inpatient psychiatric treatments [47]. For the categorical primary outcome measures, we will use the Chi-square test and multivariate logistic regression analysis to explore predictor variables for high-cost health services utilization variables of interest.

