### Study design

This is a hypothesis-driven program evaluation study that employs a mixed methods approach to evaluate the RASP. It consists of a within-subject comparison (pre- and post-evaluation study) and a controlled between-subject comparison (cohort study). The pre-and post-evaluation study will examine health services utilization data from patients attending RASP, one year before and one year after their psychiatry assessment at the program (Fig. 3a). The pre-and post-evaluation of health services utilization will also enable a comparison between RASP patients who choose to participate in the optional Text4Support RCT and those who choose not to participate in the optional Text4Support RCT.

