### Outcome measures

Primary outcome measures will include the mean differences in the frequency/duration/related costs of high-cost mental health services utilization (i.e., volume and proportion of mobile crisis visits, ED visits, hospital admissions and readmissions and associated LOS for each admission) between one year pre- and post-assessment date for same patients at RASP (within-subject comparison) and between the IG (RASP) and CG (historical data) (between-subjects comparison). Other primary outcome measures will be the mean difference in the number and proportion of total referrals booked directly for a psychiatrist and the number of calendar days for access to psychiatrists, also compared to the control group.

Secondary outcome measures include the mean difference in the frequency/duration/related costs of high-cost health services utilization one year post for patients who access the RASP and participate in the Text4Support RCT (to receive either daily supportive text messages or a single text message with a link to e-mental health resources) and patients accessing RASP but who do not participate in the Text4Support RCT. Other secondary outcome measures include a descriptive summary of the sociodemographic and clinical characteristics of the assisted population, the mean scores on the Patient Health Questionnaire 9 (PHQ-9) [38], Generalized Anxiety Disorder 7 (GAD-7) [39], World Health Organization 5 (WHO 5 Well-Being Index) [40], Brief Resilience Scale (BRS) [41], Recovery Assessment Scale (RAS) [42], Adverse Childhood Experience (ACE questionnaire) [43], Brief Substance use Craving Scale (BSCS) [44], and the Columbia-suicide severity rating scale (C-SSRS) [45], as well as the prevalence of likely MDD, GAD and low resilience. Patient overall impressions (i.e. barriers to accessing RASP, satisfaction level, likely recommend the service to others, etc.) and impressions on the experience (i.e. feelings of welcomeness, respect, enough time to talk, the problem addressed, and understanding of treatment) are part of the patient satisfaction quantitative evaluation. An in-depth evaluation of healthcare partner impressions and patient satisfaction will be obtained through qualitative key informant interviews until saturation is reached and no new themes and subthemes emerge.

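### The primary within-patient pre/post comparison is assigned unpaired tests (independent-sample t-test and Chi-square), so its standard errors and p-values will be wrong

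*Protocol article*

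**What the plan says.** The Study design section sets up a within-subject study: "The pre-and post-evaluation study will examine health services utilization data from patients attending RASP, one year before and one year after their psychiatry assessment". The Outcome measures section makes this a primary outcome, as mean differences in frequency, duration and cost of high-cost service use "between one year pre- and post-assessment date for same patients at RASP (within-subject comparison". The Hypothesis section expects the 10% reduction to appear in this comparison as well as in the one against historical controls.

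The Quantitative analysis section then fixes the tests. The sentence opens with "Primary outcomes comparing the pre-and post-enrollment health services utilization for patients accessing RASP" and says these "will be analyzed using descriptive and inferential statistical analysis, including Chi-Square and independent sample t-tests". The next sentence gives the control-group comparison its own method: "For the primary outcome involving control populations, pre- and post-enrollment health services utilization variables will initially be compared using an analysis of covariance (ANCOVA". The Text4Support comparison also has its own ANCOVA. No paired t-test, signed-rank test, McNemar test, mixed model or GEE is named anywhere for the pre/post contrast.

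**The concern.** The pre-year and post-year values come from the same people. The variance of the mean change therefore contains a covariance term, which an independent-sample t-test sets to zero. A Chi-square test comparing the proportion of users before and after makes the same error for a binary outcome.

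If heavy users in one year tend to be heavy users in the next, which is plausible but not shown in the article, the covariance is positive and the planned standard error is too large. Confidence intervals would be too wide, and a real change in a less frequent component, such as mobile crisis visits or readmissions, could be reported as no change. The plan would also give up the gain in precision that using each patient as their own control offers.

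**Working it through.** **Which comparison the tests belong to.** The sentence naming them concerns RASP patients only, before versus after enrolment. The control and Text4Support comparisons each have an ANCOVA. The Chi-square named later in the same section, for categorical primary outcomes, serves to explore predictors, which is a different use. The unpaired tests are therefore tied to the within-subject contrast.

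**The plan's own figure.** The Sample size considerations section uses "a power of 90% (β = 0.1) and a two-sided significance level of α = 0.05", "at least a 10% reduction in high-cost health services utilization" and a mean of 10 with SD 1, and arrives at 525 per group. That is for RASP versus control; no sample size or power is given for the pre/post contrast. The 525 does not follow from those inputs: 2 × (1.96 + 1.2816)² × (1/1)² = 21.01, or 22 per group. It matches a standardised difference of 0.2: 2 × 10.51 / 0.2² gives 526, which implies an SD of about 5. That is a separate problem, and nothing below depends on it.

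**Inputs for the check.** Two-sided alpha of 0.05 and 90% power come from the article. The pre/post correlation r is not given and is an assumption, shown over a range. Pre and post variances (σ²) are assumed equal.

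**Formulas.** With n patients:

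- Variance of the mean change, paired: 2σ²(1 − r)/n. Variance used by the independent test: 2σ²/n.
- Ratio of standard errors, independent to paired: 1/√(1 − r).
- Actual two-sided size of the independent test: 2 × [1 − Φ(1.96/√(1 − r))].
- Power of the independent test where the paired test has 90%: Φ(3.2415 − 1.96/√(1 − r)), with 3.2415 = 1.96 + 1.2816.

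Example at r = 0.5: 1/√0.5 = 1.414. Size is 2 × [1 − Φ(2.772)] = 0.0056. Power is Φ(3.2415 − 2.772) = Φ(0.470) = 0.68.

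| assumed r | SE ratio | actual size (nominal 5%) | power where paired has 90% |
|---|---|---|---|
| −0.2 | 0.91 | 7.4% | 93% |
| 0 | 1.00 | 5.0% | 90% |
| 0.2 | 1.12 | 2.8% | 85% |
| 0.3 | 1.20 | 1.9% | 82% |
| 0.5 | 1.41 | 0.6% | 68% |
| 0.7 | 1.83 | 0.03% | 37% |

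**Check on skewed counts.** Paired gamma-Poisson counts with no true change were simulated for 2500 patients, 2000 runs per setting. Rejection rates at nominal 5%:

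| pre/post correlation (about) | independent t | paired t | unpaired Chi-square, any use | McNemar |
|---|---|---|---|---|
| 0.33 | 1.3% | 4.6% | 2.2% | 5.0% |
| 0.67 | 0.05% | 4.8% | 0.9% | 4.9% |
| 0.87 | 0.0% | 4.6% | 0.25% | 5.4% |

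The paired tests hold their level and the unpaired ones do not, so the result is not an artefact of the normal formulas.

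**The case against.** Several points on the other side have weight.

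- **The error is conservative if r is positive.** It does not then create false claims of benefit, and the mean change is unaltered. This is right. The sign of r is itself an assumption, however, and at r = −0.2 the size rises to 7.4%.
- **The study is large.** The power column starts from a paired power of 90%, which is not necessarily this study's position. With 2500 patients and a standardised difference of 0.2, even the unpaired test has z = 0.2/√(2/2500) = 7.07, hence power above 99.9%. This stands for the aggregate outcome at that effect size. It gives less assurance for weaker individual components, and only consenting patients enter the analysis.
- **Equal variances are assumed.** If the post-year SD were half the pre-year SD, the ratio at r = 0.5 would be √(1.25/0.75) = 1.29, with size about 1.1% and power about 76%. The figures move, but the test stays wrong.
- **The Chi-square part is partly inferred.** The article does not say Pearson and defines no any-use variable, and McNemar's statistic is itself referred to a chi-square distribution. The t-test is the firm error; the Chi-square needs at least to be specified.
- **Length of stay per admission behaves differently.** A patient may have no admission in one year and several in another. Repeated admissions within a patient can make an independent test's standard error too small. The direction given above does not carry over to that component.
- **The list is open-ended and the article is condensed.** That could explain leaving a paired test out. It does not explain naming independent-sample tests for this contrast.

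**Conclusion.** The concern holds. The tests named for a primary comparison contradict its within-subject design, and the article names no valid alternative for it. The standard error and p-value are right only at r = 0. For assumed r between 0.3 and 0.7 with equal variances, the standard error is inflated 1.20 to 1.83 times and the true error rate falls to between 1.9% and 0.03%. The corresponding power, against a paired 90%, is 82% down to 37%. The size depends on an unstated correlation, and at about 2500 patients the loss of power matters mainly for small effects. The invalid intervals and p-values remain at any sample size. This must be corrected before analysis.

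**What to change.** In the Quantitative analysis section, replace the unpaired tests for the RASP pre/post comparison with paired methods:

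- **Counts, total days and costs per patient-year:** a paired t-test with a bootstrap confidence interval, or a GEE or mixed count model with log link and patient as the cluster. The log-link model estimates percentage change directly, which is the form of the 10% hypothesis.
- **Any ED visit, any admission and similar yes/no outcomes:** McNemar's test or conditional logistic regression.
- **Length of stay:** either define it as total days per patient-year and pair it, or keep it per admission and use a model clustered on patient, which also handles repeated admissions.

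The cost is about one sentence, plus a clause saying which length-of-stay definition applies. The data are unchanged and the methods are available in the named software.
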